##### Objective 5: To conduct exploratory analyses to examine whether caregiver baseline characteristics (e.g., gender, age, financial stress and food insecurity, caregiver stress and depression, and parenting behaviour) are potential moderators of component effectiveness

In exploratory analyses, we will test the potential moderation of each component by socio-demographic information such as caregiver gender and age, as well as baseline severity of caregiver stress, depression, financial stress, and parenting behaviours. If appropriate, stratified analysis or effect modification will be used, adding interaction terms for the treatment component and the potential moderator [76] and considering separating effect modification into contextual and person-level effects.

#### Cost-effectiveness (Objective 6)

The study will follow the two-stage cost-effectiveness analysis procedure described in Bernstein, Dziura [77]. In the first step, we will build an incremental cost-effectiveness table where the total cost associated with each of the 8 experimental conditions will be compared against the average number of workshops completed within those conditions. Conditions that are clearly dominated in terms of cost to engagement ratio will be dropped, without regard to the statistical significance. In the subsequent more refined analysis step, the marginal cost of delivering each level of the constituent intervention components will be compared to the marginal effectiveness of the component; effectiveness will once more be defined in terms of number of workshops completed. The reason for considering this primary outcome in particular is that unlike the outcome associated with the higher form of engagement (that is, engagement with the skills, i.e. home-practice activities), it is not a self-reported measure. Incremental cost-effectiveness ratios will be estimated alongside 95% confidence intervals.

#### Qualitative analysis (Objective 7)

A novel feature of this study is the use of qualitative interviews to assess facilitators of and barriers to engagement. The aim of this approach is to ensure that intervention components are considered acceptable and feasible by participants. Qualitative interviews will be audio-recorded, transcribed, and then translated into English. Researchers will independently review a sample of transcripts and draw on the research questions and early engagement findings to generate a coding framework. The data will then be jointly reviewed to reach a consensus on the coding scheme. Thereafter, researchers will analyse the data thematically by identifying overarching themes, relationships, and concepts [78]. Data will be analysed with the support of QSR-NVivo qualitative analysis software.

#### Analytic strategy for selecting final intervention package (Objective 8)

The optimisation criteria for this study are to select the most effective, cost-effective, and feasible component levels for inclusion in the optimised intervention. Using the decision-making framework outlined by Collins and colleagues [51], we will apply the following selection procedures. First, we will examine the main effects to determine whether a component has an effect overall, averaged across the other two components. If a significant differential effect is detected, we will tentatively select the effective component level. If a component has no main effects or a negative effect, we will tentatively retain the lower component level or the level hypothesised to perform worse. If a component level has a main effect, its cost-effectiveness will then be examined. We will then draw on qualitative findings to examine the acceptability and feasibility of the retained component level. Component levels found to be acceptable and feasible in the interviews and FGDs with participants (that are also effective and cost-effective) will be included in the final optimised intervention (Fig. 3).

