#### Cost outcomes

Costs related to two of the three intervention components will be considered in this study. These include all costs associated with delivering the support component of the intervention, as well as the digital literacy training component. These costs will be collected by the relevant implementing staff using cost diaries. Costs will include money and time spent on programme delivery, i.e. materials and staff-time required for training, preparation, delivery, and coordination of activities. Costs associated with the development of the app are being excluded, since real-world deployments will effectively happen at zero-marginal cost, excluding the cost associated with content adaption. This is because the app has been developed to be completely self-contained, such that no additional supporting infrastructure is needed for routine rollout. In addition, costs incurred by participants (e.g., time spent using the app), and the evaluation of the intervention will be excluded from analyses, as the focus of this study is to understand scale-up cost, feasibility and effectiveness.

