#### Primary and secondary outcomes (Objective 1 and 2)

Generalised linear mixed effects modelling will be used to examine the main effect of each component level (e.g., those receiving sequential workshops versus those receiving non-sequential modules) on primary and secondary engagement outcomes. This approach includes a random intercept for clusters which will account for nesting of participants in neighbourhoods. The appropriate error distribution and link function will be selected for each outcome variable (e.g., overall app launches will be parametrised using a Poisson distribution; proportion of workshops completed will be parameterised using a Binomial distribution; proportion of home practice activities will be parameterised using a Binomial distribution). Main effects will be modelled as fixed effects and evaluated at the 0.05 significance level along with 95% confidence intervals. To assist the interpretation of effects, effect coding (where component levels take on the value of -1 or 1) may be applied [51, 74]. The regression will also include baseline covariates centred on the sample mean including caregiver gender and age, adolescent age, financial stress, and parenting behaviour such as child maltreatment.

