#### Statistical power and sample size considerations for primary objectives

Given our focus on participant engagement and the intricate nature of the study design, we opted for a simulation-based approach to ascertain the appropriate sample size and statistical power [75]. We generated data for a 16-cluster randomised experiment with eight unique experimental conditions, varying the number of participants within each cluster (mean of 40, standard deviation of 8). We built the analysis model outlined above for each of the primary outcomes (i.e., overall app launches, proportion of sessions completed, and proportion of home practice activities started), estimating engagement rates and model parameters based on existing digital parenting intervention research (e.g., [32]), digital mental health interventions implemented in real-world settings (e.g., [36]), the original PLH for Teens cluster RCT in South Africa [13], and plausible scenarios based on observations from the ParentApp feasibility pilot. For each outcome model, 10,000 datasets were generated.

We estimated the minimum effect sizes needed to achieve ≥ 80% power for each of the primary outcomes while taking into account clustering and assuming an alpha level of 0.05. Poisson and Binomial distribution models were fitted for count and factor outcomes, respectively. Effect sizes were calculated as incidence rate ratios (IRRs) for Poisson distribution models and odds ratios (ORs) for Binomial distributions, which were averaged across all 10,000 replications. For overall app launches, the mean IRRs were 1.14 for support (WhatsApp), 0.91 for app design (sequential workshops), and 1.21 for digital literacy (on). For the proportion of sessions completed, the mean ORs were 2.18 for support (WhatsApp), 0.48 for app design (sequential workshops), and 2.35 for digital literacy (on). For the proportion of home practice activities started, the mean ORs were 3.13 for support (WhatsApp), 0.67 for app design (sequential workshops), and 2.31 for digital literacy (on). Based on these results, we determined that a sample of 640 participants would be sufficient to detect a significant effect in each of the primary outcomes.

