#### Exploratory analyses

##### Objective 3: To conduct exploratory analyses to examine whether there are any interaction effects between components on primary and secondary engagement outcomes

We anticipate that there will be some interactions (synergistic effects) between component levels. In exploratory analyses, we will examine a fully saturated generalised linear mixed effects model which includes all three main component effects, as well as two-way and three-way interactions. This model will be replicated for each of the primary and secondary outcomes. However, interaction effects will not be considered in the final component level selection process due to potential power constraints.

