
##### Mitigating potential harm from intervention

We have also considered the potential risk of harm from participating in the intervention, and will be monitoring this throughout the project [79]. Participation in the parenting programme may potentially cause psychological harm for caregivers, particularly when they confront difficult experiences from their own childhood or deal with intimate partner violence at home. However, past research on parenting interventions, including numerous randomised trials conducted in LMICs [11], have consistently shown no evidence of harm and abundant evidence of benefits for both parents and children, as well as high levels of parent satisfaction. To ensure a comprehensive understanding of the potential outcomes of the parenting programme, this study will explicitly examine both the benefits and risks of the intervention. Our statistical analysis plan includes two-tailed tests to assess the differences between groups and examine potential positive and negative effects of the intervention. We will also use qualitative analysis to explore the experiences and perspectives of participants regarding the intervention and its effects.

We anticipate no direct harm as a result of withdrawing from the intervention, as participation in the programme is completely voluntary, with no direct penalties for non-participation. Furthermore, other studies, including evaluations in other low-resource settings [11], have shown no evidence of harm resulting from the termination of parenting interventions. In the unlikely event of significant harm being observed in any of the intervention conditions, we will suspend the implementation of the programme until the harm has been adequately addressed, and the programme has been modified accordingly.

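### When the app-design test is not significant, the selection rule keeps the design hypothesised to be worse, although the trial measures no cost saving from doing so

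*Protocol article*

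**What the plan says.** The section on selecting the final intervention package (Objective 8) first looks at main effects: "If a significant differential effect is detected, we will tentatively select the effective component level". For a component with no main effect, or a negative one, the instruction is: "we will tentatively retain the lower component level or the level hypothesised to perform worse". Cost-effectiveness is then examined for levels that have a main effect, and the interviews and focus groups serve as an acceptability and feasibility check.

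Three other sections bear on app design:

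- *Hypotheses*: the non-sequential modules are expected to engage caregivers more than the sequential workshops, so the level hypothesised worse is the sequential one.
- *Cost outcomes*: "Costs related to two of the three intervention components will be considered in this study". These are support and digital literacy training. App development cost is excluded, and roll-out is treated as having practically no marginal cost, apart from adapting content.
- *Cost-effectiveness (Objective 6)*: the first step tabulates cost against workshops completed for the eight conditions and removes clearly dominated ones, whether or not the differences are significant.

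On testing, the protocol says: "Main effects will be modelled as fixed effects and evaluated at the 0.05 significance level along with 95% confidence intervals". It also says: "Our statistical analysis plan includes two-tailed tests to assess the differences between groups".

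**The concern.** Keeping the lower level after a null result is a parsimony rule: do not pay for something not shown to work. It fits components that are either delivered or not. App design is not of that kind. Caregivers receive one design or the other, and the trial records no cost that differs between them. The rule therefore demands significance before adopting one of two alternatives and offers nothing measured in return.

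The output of Objective 8 is the package for the next RCT. If the non-sequential design is better but the test misses 0.05, that RCT would evaluate the app in the design that engages caregivers less. The later steps of the procedure would not correct this. The cost step applies to levels with a main effect, and the qualitative check looks at the retained level without comparing it with its alternative on engagement.

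**Working it through.** **Inputs**

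- Two-sided test at 0.05, critical value 1.96 (*Primary and secondary outcomes*; *Mitigating potential harm from intervention*).
- Design power: "We estimated the minimum effect sizes needed to achieve ≥ 80% power for each of the primary outcomes". For app design on proportion of sessions completed, the mean OR given is 0.48.
- Sample size: 16 clusters × 40 = 8 conditions × 80 = 640, which agrees with the protocol.
- The simulated power cannot be reproduced, because the article does not give the baseline rates or the cluster variance. I therefore take power to be exactly 80% at the design effect. This is an assumption.
- One test decides, and its statistic is approximately normal with mean z (true effect divided by its standard error) and variance 1. This is also an assumption.

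**Formulas, with the non-sequential design truly better**

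- Written rule: non-sequential is selected only if it is significantly better. P(keep worse design) = 1 − Φ(z − 1.96).
- Choice by the estimate when the test is not significant: if test and estimate use the same outcome, this amounts to choosing by the sign of the estimate. P(keep worse design) = Φ(−z).

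**Effects considered, expressed as ORs for sessions completed**

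- 80% power: z = 1.96 + 0.84 = 2.80. Here ln(1/0.48) = 0.734, so the implied standard error is 0.734/2.80 = 0.262.
- 50% power: z = 1.96, so the OR is exp(−1.96 × 0.262) = 0.60.
- Half the design effect on the log scale: z = 1.40, so the OR is exp(−0.734/2) = 0.69.

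| True effect | z | Written rule keeps worse design | Choice by estimate keeps worse design |
|---|---|---|---|
| 80% power (OR 0.48) | 2.80 | 1 − Φ(0.84) = 20% | Φ(−2.80) = 0.3% |
| 50% power (OR about 0.60) | 1.96 | 1 − Φ(0) = 50% | Φ(−1.96) = 2.5% |
| Half the design effect (OR about 0.69) | 1.40 | 1 − Φ(−0.56) = 71% | Φ(−1.40) = 8% |

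A t reference distribution with 12 degrees of freedom (16 clusters less 4 coefficients) gives nearly the same: 20% against 0.1% at the 80%-power effect, and 71% against 6% at half of it.

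**The price if the sequential design is truly better**

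- Choice by the estimate picks the non-sequential design wrongly with probability Φ(−z), which is 2.5% at the 50%-power effect.
- The written rule does so with probability Φ(−z − 1.96) = Φ(−3.92), below 0.01%.
- With no true difference, the written rule keeps the sequential design 97.5% of the time and the estimate splits 50:50. Neither choice then costs engagement.

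**The two procedures side by side**

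Take two conditions that differ only in app design. Their measured costs should be similar, since nothing collected depends on the design. Under *Cost-effectiveness (Objective 6)*, the one with clearly fewer completions can be removed on its estimate alone. Under *Analytic strategy (Objective 8)*, a non-significant main effect keeps the sequential design whatever the estimate shows. The two can point in opposite directions, and the article does not say which prevails.

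**The case against.** **The default is only tentative, and dominance may catch it.** The rule is provisional, an acceptability check follows, and the dominance step could remove sequential conditions on their estimates. But the article does not connect that step to the retained level, and its Objective 8 text sends only levels with a main effect to the cost step. The objection shows a conflict between the sections without resolving it.

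**Sequential is the original design.** Staying with the established version can be a reason in itself. The selection section does not give that reason, and both versions have to be available for this trial.

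**Equal cost is not shown.** This stands. A reader might infer that both designs are free. The protocol says only that roll-out has practically no marginal cost, content adaptation aside, and it collects no costs by design. The supportable statement is that no cost difference is measured.

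**The percentages need a single deciding test.** This also stands. The selection section names no outcome, and a reader might infer that significance on any one of the three primary outcomes is enough. The article does not say so, and both the decision diagram (Fig. 3) and the statistical analysis plan are unseen, so the any-outcome reading is no part of this point. If it did apply, with equal power on each outcome and assumed correlations of 0 to 0.7, the worse design would be kept 0.8% to 8% of the time at 80% power and 13% to 31% at 50% power. The loss would be smaller.

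**Interactions.** A reader might also fault the rule because the protocol says "We anticipate that there will be some interactions (synergistic effects) between component levels" and yet "interaction effects will not be considered in the final component level selection process due to potential power constraints". That is a disclosed choice with a stated reason. An interaction coefficient half the size of the 80%-power main effect would have only about 27% to 29% power. Statisticians would differ on it, and it is not an error in the plan.

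**Conclusion.** The point holds for app design only. The default has a cost rationale for support and training and no measured one for app design, and it sits badly with the protocol's own dominance step.

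With a truly better non-sequential design, the written rule keeps the worse design 20% of the time at the 80%-power effect and 50% at the 50%-power effect, against 0.3% and 2.5% when the estimate decides. These figures assume one deciding test, an approximately normal statistic and exactly 80% power at the design effect. They describe the rule's behaviour and do not predict this trial's result. The finding that the default saves no measured cost rests on the text alone and needs none of these assumptions.

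**What to change.** In *Analytic strategy for selecting final intervention package (Objective 8)*:

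1. Limit the default of retaining the lower level to support and digital literacy training.
2. For app design, when the main-effect test is not significant, tentatively select the level with the better estimated proportion of workshops or modules completed. Workshops completed is already the effectiveness measure in the cost-effectiveness analysis. Apply the same acceptability and feasibility check as for the other components.
3. State how this choice fits with the dominance step under Objective 6, and which prevails if they disagree.

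This takes about three sentences and no further data or participants. The downside is that if the sequential design is truly better, the estimate will sometimes point the wrong way: 2.5% of the time at a 50%-power effect, against almost never under the present default. If the sponsor prefers to keep the sequential default for another reason, such as continuity with the original app, that reason should be written into the rule.

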**Fig. 3 Fig3:**
[figure not shown]
Analytic strategy for selecting final component levels for subsequent RCT

### Oversight and monitoring

#### Trial oversight

A Trial Steering Committee (TSC) has been assembled and will meet quarterly to ensure that the study is conducted with rigour. The trial coordinating team, composed of the Principal Investigators, trial managers, and key members from our partner organisations will meet regularly to oversee the management of research activities.

#### Data monitoring

Given that this is a low-risk intervention (there were no safety concerns in the ParentApp pilot study or any of the PLH effectiveness trials), no external data monitoring committee will be formed. Data safety and monitoring will be undertaken by the trial coordinating team. However, should the TSC deem it necessary, a data monitoring committee will be assembled during the study who will have access to interim analyses and make any final decisions regarding trial termination.

#### Ethical considerations and consequences of participation

##### Ethical issues regarding staff

All staff have prior experience working on community research projects in similar communities to our study. Nevertheless, conducting research in vulnerable communities can be mentally challenging and potentially harmful. As such, all research assistants will be trained in awareness and safety measures, and will not be required to undertake assessments in situations where they feel uncomfortable or unsafe. Additionally, staff will travel in pairs when working in areas that may be less safe.

Moreover, we recognise that research with vulnerable families can be emotionally challenging due to the disclosure of sensitive information. We will conduct weekly debriefing meetings with research personnel to discuss any potentially distressing events that may have occurred during data collection.

##### Potential of harm to participation

This study is committed to upholding the universal principles of human research ethics (respect, beneficence, and justice) throughout all stages of the trial. As the focus of the study is to enhance caregiver engagement in a digital parenting programme for socioeconomically vulnerable families, we believe that the potential benefits, such as reducing the risk of child maltreatment and improving family well-being, outweigh any potential harm to participants. Nevertheless, we acknowledge the possibility of harm at two levels: participation in the study and participation in the intervention.

##### Potential harm from the study

Participants may experience emotional distress brought on from disclosing challenging emotions and experiences during interviews, FGDs, and when filling in the self-administered outcome questionnaires. All interviewers will be trained and experienced in working with vulnerable families. Our research team also includes a Tanzanian community health specialist, [name], who is skilled in child and adolescent health, public health, and community health. [name] will be available to discuss or supervise discussion of any issues that may arise with the participants following the interviews. If there is a need for a participant to access more extensive support (such as seeing a counsellor or attending a clinic), we will provide direct referrals to relevant service providers through partnerships with local organisations. Additionally, direct referrals to social services will also be available through the implementing partner and intervention facilitators, should risk of harm become apparent during the group-based onboarding session or any other stage of the study.

All research personnel, including research assistants and facilitators, will be trained in ethical procedures and protocols concerning research with human subjects. During the consent stage, we will inform all participants that everything said will be confidential unless it becomes clear that the participant and/or a family member are at risk of harm. We will also inform participants that they have the right to refuse to answer any questions that they feel uncomfortable with and may stop the interview or withdraw from the study at any time without any negative consequences.

